**8. ASSOCIATED TREATMENTS AND PROCEDURES**

**8.1. AUTHORIZED ASSOCIATED TREATMENTS/PROCEDURES**

**8.1.1. AUXILIARY MEDICATIONS**
Not applicable.

**8.1.2. OTHER TREATMENTS/PROCEDURES**
Patients may continue any treatments initiated prior to the start of the study.

**8.2. PROHIBITED ASSOCIATED TREATMENTS/PROCEDURES**
No therapeutic intervention for SCD is allowed during the participant’s participation in the study.

**9. STUDY CONDUCT**

**9.1. STUDY TIMELINE**

- Inclusion period duration: 18 months
- Participation duration per participant: 1 month
- Total study duration: 19 months

**9.2. PARTICIPANT FOLLOW-UP SUMMARY TABLE**

| **Stage** | **Pre-inclusion T0 (0 to -7 days)** | **Visit 1 Inclusion T0** | **Visit 2 Follow-up T15d (+/-5d)** | **Visit 3 End-of-study T30 (+/-5d)** |
| --- | --- | --- | --- | --- |
| Informed consent | ✓ |  |  |  |
| Clinical examination | ✓ |  |  |  |
| Temporal bone CT (S) | ✓ |  |  |  |
| VAS pulsatile tinnitus (R) |  | ✓ | ✓ | ✓ |
| VAS autophony (R) |  | ✓ | ✓ | ✓ |
| VAS sound-induced balance disorders (R) |  | ✓ | ✓ | ✓ |
| VAS pressure-induced balance disorders (R) |  | ✓ | ✓ | ✓ |
| Naert questionnaire (R) |  | ✓ | ✓ | ✓ |
| Electrocochleography (EcoG) (R) |  | ✓ | ✓ | ✓ |
| Ocular and cervical VEMP (R) |  | ✓ | ✓ | ✓ |
| Wideband tympanometry (WBT) (R) |  | ✓ | ✓ | ✓ |
| Evoked involuntary responses (EvI) |  | ✓ | ✓ | ✓ |

**9.3. PRE-INCLUSION/INCLUSION VISIT**

**9.3.1. CONSENT COLLECTION**
During the pre-inclusion/inclusion visit, the investigator informs the participant and answers all questions regarding the study’s objective, requirements, foreseeable risks, and expected benefits. The participant’s rights in the context of clinical research are also explained, and eligibility criteria are verified.

A copy of the information sheet and consent form is provided to the participant by the investigator. After this information session, the participant has time to consider participation. If the participant agrees, both the participant and the investigator clearly print their names, date, and sign the consent form. The consent form must be signed **before any clinical or paraclinical examination required by the study is performed**.

**9.3.2. VISIT PROCEDURE**
The pre-inclusion/inclusion visit is conducted by the investigator. Before any study-related examination, the investigator obtains free, informed, written consent from the participant (or legal representative, if applicable).

At the pre-inclusion visit, the previously performed temporal bone CT will be examined to formally confirm the SCD diagnosis.

At the inclusion visit, the following will be performed:

- Clinical examination and evaluation of cardinal symptoms (pulsatile tinnitus, autophony, sound-induced balance disorders, pressure-induced balance disorders)
- Naert questionnaire
- Electrophysiological measurements recorded twice on the healthy ear and twice on the affected ear:
  - Electrocochleography (EcoG)
  - Ocular and cervical VEMP
  - Wideband tympanometry (WBT)

**9.4. FOLLOW-UP VISITS**

**Visit 2 (15 days ± 5 days)**
During visit 2, performed on site by study staff:

- Clinical examination and evaluation of cardinal symptoms
- Naert questionnaire
- Electrophysiological measurements recorded twice on the healthy ear and twice on the affected ear:
  - Electrocochleography (EcoG)
  - Ocular and cervical VEMP
  - Wideband tympanometry (WBT)

**9.5. END-OF-STUDY VISIT**

**Visit 3 (30 days ± 5 days)**
During visit 3, performed on site by study staff:

- Clinical examination and evaluation of cardinal symptoms
- Naert questionnaire
- Electrophysiological measurements recorded twice on the healthy ear and twice on the affected ear:
  - Electrocochleography (EcoG)
  - Ocular and cervical VEMP
  - Wideband tympanometry (WBT)

**9.6. WITHDRAWAL RULES**

**9.6.1. PATIENT WITHDRAWAL FROM THE STUDY**
A participant may discontinue the study:

- By necessity, as decided by the investigator
- By personal decision: early withdrawal from the protocol

Regardless of the reason, patient care will remain the same as prior to study participation.

Participants may withdraw at any time without any specific responsibility or obligation. They are free to justify their decision. Data collected before withdrawal will be used unless the participant requests destruction.

Early withdrawals prior to visit 2 will be replaced.

**9.6.2. STUDY TERMINATION**
The study will normally end as planned in the protocol.
However, temporary suspension or early termination may occur due to:

- Significant violations of good clinical practice (GCP) compromising the primary objectives or participant safety
- Occurrence of local or global events (e.g., COVID-19 pandemic) impacting participant safety monitoring

**9.7. STUDY CONSTRAINTS AND PARTICIPANT COMPENSATION**
Study constraints are minimal (category 2, article L1121 of the French Public Health Code).
Participants may participate in another study concurrently.
No compensation is planned. Travel expenses to the study site will be covered by the study.

**9.8. COLLECTION OF BIOLOGICAL SAMPLES**
Not applicable.

**10. ADVERSE EVENTS / INCIDENT MANAGEMENT**
Adverse events, incidents, or side effects will be reported according to the applicable vigilance systems (healthcare, pharmacovigilance, hemovigilance, cosmetovigilance, etc.) in compliance with regulations.

Reporters must specify the patient is enrolled in a clinical trial and identify the specific study.

Investigators must immediately inform the sponsor of any patient safety concerns during the study.

No adverse events are expected under the study protocol.

Sponsor: CHU de TOULOUSE
Vigilance responsible: [name] [name]
[contact]
Email: [contact]

**11. STATISTICAL ASPECTS**

**11.1. SAMPLE SIZE CALCULATION**
To evaluate reliability and validity of electrophysiological indicators, the sample size was defined to estimate reliability and validity parameters with sufficient precision.

100 patients with 6 repeated measurements will allow estimation of an intraclass correlation coefficient (ICC) > 0.80 with 95% CI width < 0.10.

Additionally, 100 patients allow the following precision for correlation values:

- 95% CI width < 0.30 for Pearson correlation ≥ 0.50
- 95% CI width < 0.40 for Pearson correlation = 0

**11.2. STATISTICAL METHODS**
Data will be described overall; outliers will be identified and corrected if possible. Missing data will be described for the population.

Inclusion/exclusion criteria, patient follow-up, and reasons for early withdrawal will be described, with a flow chart for inclusions and withdrawals.

Reliability of repeated measures will be evaluated first, as it allows further validity assessment:

- Electrophysiological indicators: intra-patient reproducibility (6 repeated measures), inter-visit (3 visits), intra-visit (2 measures per visit) using Bland-Altman plots (1999) with mean bias, 95% CI, and limits of agreement. Adaptation for more than 2 repeated measures will be used for inter-visit or intra-patient reliability (Jones et al., 2011). Intraclass correlation coefficients with 95% CI will also be calculated.
- The same reliability assessment applies to 3 repeated cardinal symptom measures.

If clinical and paraclinical measures are reliable, the validity of indicators will be analyzed using the mean of 6 repeated electrophysiological measures and the mean of 3 repeated clinical symptom measures.

- Convergent validity: correlations between electrophysiological indicators on the pathological (SCD) side and symptoms (presence, intensity, Naert questionnaire)
- Divergent validity: same analyses for the healthy side
- Correlations between electrophysiological indicators, anatomical-radiological measures, symptoms, and quality of life will be described to better understand construct validity.

If inter-visit reliability does not allow use of repeated-measure means, correlations may be estimated using mixed-effect models after standardization of variables. Psychometric properties of the French-translated Naert questionnaire will be assessed (inter-item correlations, item-total correlations, Cronbach’s alpha). Factor analysis will be performed.

Test-retest reproducibility of the Naert questionnaire will be evaluated by intraclass correlation coefficient and Bland-Altman indicators (3 repeated measures across 3 visits).

Unsupervised multivariate descriptive analysis (PCA, clustering) will define patient profiles based on electrophysiological, anatomical, and symptom characteristics. Supervised modeling (partial least squares regression) may also be applied to predict symptoms from multivariable indicators (+/- anatomical indicators).

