**4.3.3. PSYCHOMETRIC EVALUATION OF THE NAERT QUESTIONNAIRE**
Using the French-translated scale, the following properties will be assessed:

- Internal consistency (Cronbach’s alpha coefficient),
- Inter-item and total-item correlation coefficients,
- Factor analysis to evaluate unidimensionality,
- Test-retest reliability across 3 repeated measures (one per visit, in clinically stable conditions) using Bland-Altman method and ICC calculation.

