**6. ELIGIBILITY CRITERIA**

**6.1. INCLUSION CRITERIA**

- Unilateral SCD formally diagnosed by high-resolution CT (≤0.5 mm slices, reconstructions in the plane of the superior semicircular canal and perpendicular plane) of the temporal bone, with no requirement for symptom severity.
- If present, SCD-related symptoms must be stable in a diagnostic and follow-up context, with no therapeutic intervention planned within 3 months of the first visit.
- Adult patient (≥18 years), able to read and understand French.
- Affiliated with or beneficiary of a social security scheme.
- Free, informed, written consent signed by the participant and investigator (at the latest on the day of inclusion and before any study-related examination).

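### The retest of the VAS and the French questionnaire assumes stable symptoms, but nothing collected at visits 2 and 3 lets real change be separated from measurement error

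*Protocol*

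**What the plan says.** Protocol section 11.2 sets out ICCs and Bland-Altman analysis for the electrophysiological measures and then adds: "The same reliability assessment applies to 3 repeated cardinal symptom measures". Retest of the French questionnaire "will be evaluated by intraclass correlation coefficient and Bland-Altman indicators (3 repeated measures across 3 visits", and section 4.3.3 describes its three scores as "one per visit, in clinically stable conditions". Section 5.1 places the questionnaire validation on the 100 included patients. No section names a stable subset for either retest.

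Four provisions support stability:
- Section 6.1: "If present, SCD-related symptoms must be stable in a diagnostic and follow-up context", with no therapeutic intervention planned in the three months after the first visit.
- Section 3.2: the repeat visits take place in a clinically stable context with no therapeutic intervention between them.
- Section 5.1: the short interval is part of the reasoning for the retest.
- Section 8.2: no intervention for SCD during participation.

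Sections 9.4 and 9.5 list a clinical examination, the cardinal-symptom evaluation, the questionnaire and the electrophysiological tests at visits 2 and 3. The table in section 9.2 ticks clinical examination at pre-inclusion only. The table's EvI row is ticked at all three visits, and the abbreviation list defines EvI as adverse event. Section 12.3 plans dictionary coding of adverse events and concomitant treatments.

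**The concern.** A retest ICC reads within-patient differences between visits as error. That is right only when the patient's true state has not moved. Electrophysiology is recorded twice per visit, so its within-visit error can be seen apart from movement between visits. The VAS and the questionnaire are taken once per visit, so their data cannot make that split.

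Some room for change remains. Visit 3 may fall up to 35 days after visit 1 (30 + 5). Section 8.1.2 says "Patients may continue any treatments initiated prior to the start of the study" and sets no minimum prior duration. Section 9.7 says "Participants may participate in another study concurrently". Section 8.2 bars only intervention directed at SCD.

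At stake is whether a sound VAS or a sound French questionnaire could be reported as less reproducible than it is. Validating the questionnaire is a secondary objective, and retest reliability is one of the properties listed for it.

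**Working it through.** **1. The plan's own precision figure.** Section 11.1 gives, for 100 patients and 6 measures, a 95% CI width below 0.10 for an ICC above 0.80. I used the F-based interval for the one-way single-measure ICC:
- F = (1 + (k − 1)ρ)/(1 − ρ)
- F_L = F / F(0.975; n − 1, n(k − 1)) and F_U = F × F(0.975; n(k − 1), n − 1)
- each ICC limit = (F* − 1)/(F* + k − 1), where F* is F_L or F_U

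With n = 100 and k = 6:
- ρ = 0.80: 0.747 to 0.848, width 0.101
- ρ = 0.81: width 0.097

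The stated figure reproduces, apart from rounding at the boundary. It concerns six measures. The VAS and questionnaire have k = 3, where the width at ρ = 0.80 is 0.1185 (0.735 to 0.854). The point does not dispute section 11.1.

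**2. What real change does to the ICC.** Inputs:
- Vb, between-patient variance, set to 1.
- Ve, error variance, = (1 − R)/R for a true retest ICC of R. For R = 0.90, Ve = 0.1111; for R = 0.80, Ve = 0.25.
- p, the share of patients whose symptoms really move between visits.
- d, the SD of that movement in between-patient SDs, modelled as independent deviations at each visit.

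The documents give no value for R, p or d. All are assumptions, shown as a range.

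Formulas:
- Observed ICC = 1/(1 + Ve + p·d²)
- Widening of the limits of agreement = √((Ve + p·d²)/Ve)

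| p | d | p·d² | ICC if R = 0.90 | Limits widen by (R = 0.90) | ICC if R = 0.80 |
|---|---|---|---|---|---|
| 0 | any | 0 | 0.900 | 1.00 | 0.800 |
| 10% | 0.5 | 0.025 | 0.880 | 1.11 | 0.784 |
| 20% | 0.5 | 0.050 | 0.861 | 1.20 | 0.769 |
| 30% | 0.5 | 0.075 | 0.843 | 1.29 | 0.755 |
| 10% | 1.0 | 0.100 | 0.826 | 1.38 | 0.741 |
| 20% | 1.0 | 0.200 | 0.763 | 1.67 | 0.690 |
| 30% | 1.0 | 0.300 | 0.709 | 1.92 | 0.645 |

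Example, second row: 1/(1 + 0.1111 + 0.025) = 0.880, and √(0.1361/0.1111) = 1.11. If the between-patient SD on the 0–100 VAS were 25 (assumed), d = 0.5 would be 12.5 points and d = 1 would be 25 points.

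**3. Precision cost of a stable subset.** With the interval in step 1, k = 3 and ρ = 0.90:
- n = 100: 0.864 to 0.928, width 0.064
- n = 80: 0.859 to 0.931, width 0.072

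**4. What the visits could supply.** The cardinal-symptom evaluation at visits 2 and 3 is the VAS, which is the measure under test, so it cannot confirm its own stability. The clinical examination has no stated stability purpose and no role in section 11.2. Treatment and adverse-event records could flag some patients likely to have changed, but would miss symptoms that moved without a recorded event or treatment change.

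**The case against.** The strongest reply is that stability is built into the design: the entry criterion, the bar on SCD intervention, the short interval, and a stated intention to retest without treatment between visits. Continuing an established treatment in a patient whose symptoms are stable favours constancy, and a concurrent study could not supply SCD treatment without breaching section 8.2. Large movements in many patients are therefore unlikely, and the lower rows of the table are pessimistic. All of this stands, and it limits the likely bias.

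It can also be said that the choice of a retest set belongs in an SAP. That holds for the definition of the set, and treatment and adverse-event data could serve it. It does not hold for the rating of change: an SAP cannot use an item that no visit collects.

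A reader might infer three stronger things that the documents do not support:
- **That stability is never looked at after entry.** Sections 9.4 and 9.5 list a clinical examination, the EvI row is ticked at every visit, and section 12.3 foresees concomitant-treatment data. What is missing is any link from these to the retest.
- **That a lowered VAS ICC would decide or bias the primary correlations.** Section 11.2 makes averaging conditional on reliability but gives no cut-off, so no shift in the ICC can be shown to change the choice. The alternative is a mixed-effects estimate of the same correlations.
- **That an unchanged-patient ICC should also govern that condition.** The means are taken over all patients, and real movement between visits is what the condition ought to detect.

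**Conclusion.** The point holds in a limited form. The retest ICC and limits of agreement for the four VAS and the French questionnaire rest on assumed stability, and with one score per visit any real change is absorbed into error. The direction is certain: a lower ICC and wider limits. The size is not derivable from the documents. For a true ICC of 0.90 it runs from no effect, through 0.88 (10% changing by 0.5 SD), to about 0.76 (20% changing by 1 SD), and further only under heavier assumptions. The entry criterion and the bar on SCD intervention make the milder end more plausible. What is affected is the questionnaire validation, a secondary objective, and the VAS reliability estimate. Low priority.

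**What to change.** - At visits 2 and 3, after the VAS and questionnaire so as not to prime the answers, add one self-rated item: SCD symptoms since the last visit are better, unchanged or worse.
- Report the retest ICC and limits of agreement for the four VAS and the questionnaire in patients unchanged at both visits, beside the all-patient values. Use the concomitant-treatment data already foreseen in section 12.3 to identify treatment changes.
- Keep the all-patient inter-visit ICC for the section 11.2 decision on averaging across visits.
- Reconcile the table in section 9.2 with sections 9.3.2, 9.4 and 9.5 on when the clinical examination takes place.

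The cost is one question at two visits, its eCRF field and some wording. The unchanged-patient interval is slightly wider: about 0.072 instead of 0.064 at an ICC of 0.90 with three visits, if 80 of 100 patients qualify. The self-rating will misclassify some patients, so the two sets of results should be read together.

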**11.3. SAFETY ANALYSIS**
Not applicable.

**12. DATA AND SOURCE DOCUMENT MANAGEMENT**

**12.1. SOURCE DATA AND DOCUMENTS**
Source data consist of all information contained in original documents, or in certified copies of these documents, related to clinical examinations, observations, or other activities conducted in the context of research and necessary for reconstruction and evaluation of the study. Documents in which source data are recorded are called source documents.

In this study, source documents will consist of patients’ medical records, questionnaires completed at each visit, and reports of audiometric recordings.

**12.2. DATA COLLECTION INSTRUCTIONS**
All information required by the protocol must be recorded in the case report forms (CRFs), and an explanation must be provided for any missing data. Data must be collected as obtained and transcribed neatly and legibly into the CRFs.

Data will be collected in an electronic case report form (eCRF).

**12.3. DATA MANAGEMENT AND FLOW**
All information required by the protocol and necessary for evaluating study objectives will be recorded in the eCRF. Investigators or designated personnel are responsible for data entry into the eCRF. Investigators are responsible for ensuring data accuracy and signing the relevant pages.

The implementation and management of the eCRF will be handled by the USMR of CHU Toulouse. Data managers will be responsible for data cleaning for statistical analysis, and a data validation plan will be prepared.

Data managers will also code medical history and adverse events entered into the eCRF according to MedDRA, and concomitant treatments according to the WHO Drug dictionary. Versions of MedDRA and WHO Drug dictionaries will be defined at the start of the study by the sponsor. Data management software used is ENNOV CLINICAL.

**12.4. DATA CONFIDENTIALITY**
In accordance with applicable laws, all personnel with direct access to source data will take all necessary precautions to ensure confidentiality of information relating to experimental drugs, research participants, their identity, and study results. These personnel, like the investigators themselves, are bound by professional confidentiality.

During or after the study, data collected from participants and transmitted to the sponsor will be anonymized. Names and addresses must not be included.

Participants will be identified by a patient number corresponding to the center number followed by the patient’s inclusion order within that center.

The sponsor will ensure that each participant has given written consent for access to personal data strictly necessary for quality control of the study.

**12.5. STORAGE OF STUDY DOCUMENTS AND DATA**
The following documents will be archived by the investigator according to Good Clinical Practice, the French decree of 11 August 2008, and European regulations on medicinal products:

- For 15 years following the end of the study (for research not involving products mentioned in Article L.5311-1 of the Public Health Code):
  - Protocol and any amendments
  - Case report forms (copies)
  - Source documents of participants who have signed consent
  - All other study-related documents and correspondence
  - Original signed informed consent forms

These documents are the responsibility of the investigator during the regulatory retention period. No movement or destruction may occur without the sponsor’s agreement. After the retention period, the sponsor will be consulted regarding destruction. All data and documents may be subject to audit or inspection.

Study data will be accessible to authorized personnel from CHU Toulouse for two years after the last publication of results, and will be archived for 15 years after study completion in accordance with applicable regulations.

**12.6. DATA TRANSFER**
Data management is handled by [name of structure]. Conditions for transfer of all or part of the study database are determined by the sponsor and formalized in a written contract.

**13. MONITORING AND QUALITY ASSURANCE**

**13.1. DATA ACCESS**
Participation in the protocol implies that investigators will make available the documents and individual data strictly necessary for study monitoring, quality control, and audit to authorized personnel, in accordance with applicable laws and regulations.

**13.2. QUALITY CONTROL**
A clinical research associate (CRA) appointed by the sponsor will regularly visit each study site during study setup, periodically during the study, and at study completion. During these visits, and according to the risk-based monitoring plan (participant, logistics, impact, resources), the following will be reviewed:

- Informed consent
- Compliance with the protocol and defined procedures
- Data quality in CRFs: accuracy, missing data, consistency with source documents (medical records, appointment books, lab results, etc.)
- Management of any study products

Each visit will result in a written monitoring report.

**13.3. AUDIT AND INSPECTION**
An audit may be conducted at any time by sponsor-appointed personnel independent of study staff to verify participant safety, regulatory compliance, and data reliability.

An inspection may also be performed by a competent authority (e.g., ANSM in France, EMA for European trials). Audits and inspections can apply at any stage, from protocol development to publication and data archiving.

Investigators agree to comply with sponsor requirements for audits and competent authority inspections.

